### Ethical Considerations

This study was reviewed and approved by the institutional review board (IRB) of Hallym University Chuncheon Sacred Heart Hospital (CHUNCHEON 2025-03-004-004) and has been formally registered with the Clinical Research Information Service of the Korea Disease Control and Prevention Agency, a World Health Organization–recognized primary registry (registration KCT0010968).

The research team will provide each participant with a detailed explanation of the clinical procedures, expected treatment effects, and therapeutic services provided. This explanation will take approximately 30 minutes, after which written informed consent will be obtained. Participants will then receive access to the DTx app, followed by an orientation session on its use, which will also last approximately 30 minutes. Therefore, the total explanation and orientation period will be of approximately 1 hour.

During the course of the trial, each participant will be assigned a unique study identification number, which will be recorded in the electronic case report form for monitoring and data management purposes. All data collected during the study will remain confidential and will be securely stored in accordance with the IRB-approved protocol.

As the study involves no invasive procedures and the investigational DTx app is noninvasive, no serious risks are anticipated; therefore, no independent data monitoring committee has been established, as approved by the IRB. Nevertheless, internal investigators will continuously monitor participants’ treatment progress throughout the trial.

Participants enrolled in the D-STOP clinical trial will receive modest compensation for their participation. Compensation is provided at 3 time points across the 7 scheduled study visits (including the enrollment visit): at the baseline visit, the fifth visit, and the final seventh visit. Unlike the contingency management approach used in RESET-O, these incentives are not delivered immediately in response to treatment adherence or abstinence outcomes. Instead, they serve solely as nominal compensation for participation in the clinical study. Each compensation is KRW 50,000 (US $35) per visit, and participants will receive a total compensation of KRW 150,000 (US $105).

## Results

The study has been funded for a 3-year period starting on April 1, 2023. This study has progressed to the initiation of the confirmatory clinical trial following approval from the Ministry of Food and Drug Safety and an IRB amendment review at Hallym University Chuncheon Sacred Heart Hospital in April 2025. Data collection began on August 4, 2025, and is expected to be completed by November 30, 2026. As of March 6, 2026, a total of 65 patients have been enrolled, and an interim analysis has been conducted based on the data available at the time of analysis. However, statistical significance could not be established due to the limited sample size. A final analysis will be conducted once all data have been collected, and the results are expected to be reported in spring 2027.

## Discussion

The aim of this study is to evaluate the efficacy, acceptability, and feasibility of a CBT-based DTx intervention for individuals with SUD. Previous studies have demonstrated that CBT provides significant therapeutic benefits for patients with SUD, and RESET-O—the first DTx intervention of its kind—showed considerable success in its confirmatory clinical trial. Furthermore, the dissemination of DTx as a means of delivering remote treatment is highly beneficial for patients with SUD in South Korea. Although RESET-O ultimately faced limitations in the United States due to insurance-related issues, the Korean health care environment provides a more favorable setting: insurance barriers are comparatively easier to resolve, and patients do not face heavy financial burdens in accessing therapeutic devices. Unlike RESET-O, which primarily relied on one-way delivery of CBT educational videos and workbooks, D-STOP has the advantage of an interactive treatment model that enables patients to build personalized treatment behavior patterns through engagement with the program. In addition, D-STOP equips patients with immediate coping strategies to reduce cravings and improve daily lifestyle management, thus offering a wider range of therapeutic options.

Despite these strengths, this study has several limitations. First, the DTx format may increase the burden on patients. In traditional face-to-face CBT, the therapeutic effect often depends on the clinician’s level of expertise—sometimes alleviating patient burden—whereas DTx place more responsibility on patients themselves. However, because CBT can be ineffective for some patients when clinicians fail to explain concepts clearly, we addressed this limitation by simplifying CBT terminology within D-STOP to ensure accessibility and comprehension. A usability evaluation was also conducted to confirm that patients could easily understand and use the intervention.

Another limitation is that participants were not stratified by severity of SUD. Clinicians often consider even using drugs a single time as an indicator of severe clinical risk. For research purposes, ideally, treatment efficacy should be validated across more finely stratified subgroups; however, recruiting participants with SUD in South Korea presents practical difficulties. Unlike in the United States or other countries where research and treatment for SUD are more advanced, South Korea is only beginning to initiate systematic clinical research in this field, and drug use has only recently emerged as a major social issue. Nevertheless, this study may serve as a foundation for future research on SUD treatment in South Korea, laying the groundwork for subsequent studies to be conducted with greater precision and more rigorous methodologies.

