### Design

Using a prospective design, we will collect longitudinal data on patients with SUD for subsequent analysis. Participants will be assigned in a 1:1 randomized fashion to a control group (TAU) or an experimental group (TAU+D-STOP). The trial will be conducted in an open-label manner. The primary aim is to demonstrate the superiority of the experimental arm over the control arm in treatment efficacy. Outcomes will be derived by integrating quantitative and qualitative data sources, including measures captured within the D-STOP app and standardized diagnostic and assessment instruments.

The meaning and implementation of TAU may vary across different medical specialties. In this study, TAU refers to maintaining the medications and treatment approaches that participants were receiving prior to enrollment in the clinical trial. With respect to medications, participants are allowed to reduce the dosage or discontinue previously prescribed medications during the study period; however, increasing the dosage or introducing new medications is not permitted.

Regarding psychosocial treatments, participants engaged in psychosocial intervention programs prior to enrollment (eg, Narcotics Anonymous meetings or 12-step addiction recovery programs) are allowed to continue participating in them. However, the initiation date of the psychosocial treatment program is required to precede the start date of participation in this clinical trial. To minimize potential confounding effects, preference is given to enrolling individuals who are not actively participating in such programs.

In addition, TAU in this study is limited to patients receiving outpatient care only. During the clinical trial period, the total number of hospital visits is scheduled to be 7. If a participant receiving outpatient care requires hospitalization during the trial period, this is considered a relapse-related event and recorded as a notable clinical occurrence; however, such cases are not classified as study withdrawal.

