### Participants

This multicenter study is being conducted at 4 medical institutions in South Korea that provide treatment for SUD. Participants will be recruited at university hospitals and general hospitals that include departments of psychiatry using both in-hospital posters and external (community-facing) advertisements.

This study aims to recruit 118 participants across 4 regions in South Korea (Seoul, Daegu, Chuncheon, and Changnyeong) based on estimates from prior research on the required sample size to demonstrate superiority (Textbox 1).

The clinical trial will last 12 weeks, with a total of 7 visits. Each visit window allows for –5 to +5 days from the scheduled date. Participants who fail to attend within this window will be considered to have discontinued the study (Table 1).

Textbox 1.Inclusion and exclusion criteria.

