**Inclusion criteria**
Adults aged 19 years or olderFulfillment of the diagnostic criteria for substance use disorder according to the *Diagnostic and Statistical Manual of Mental Disorders, Fifth Edition* [26] and diagnosis under the *International Classification of Diseases, Tenth Revision*, F11, F12, F14, F15, or F19 categories [27]At screening, completion of the Drug Abuse Screening Test–Korean Version [28]Having initiated psychiatric treatment within 30 days prior to screening and intention to continue treatment for at least 3 monthsSelf-reported history of drug use within 30 days prior to screening (or within 60 days if recently discharged from a controlled environment)Ability to read and write Korean without difficultyAbility to use a smartphone and mobile app without difficultyVoluntary provision of written informed consent after receiving sufficient explanation of the studyNo history of dementiaFor women of childbearing age, agreement to use medically acceptable contraception during the study periodIn special cases, legally authorized representatives may consent on behalf of participants; such participants are also eligible

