### Data Analysis

All data collected in this trial will be analyzed based on the entire screened population. The number of participants excluded from the safety set and the reasons for exclusion will be reported relative to all enrolled participants. Exclusions from the full analysis set will be described relative to the safety set, and exclusions from the per-protocol set will be described relative to the full analysis set. The primary efficacy analysis will be conducted on the full analysis set according to the intention-to-treat principle.

Participants who discontinue the study prematurely (dropouts) will be included in the analysis in accordance with the intention-to-treat principle. Missing outcome data will not be imputed. If missing values occur in outcomes related to abstinence status, the participant will be considered as having failed (failure) for the purpose of analysis.

For efficacy analyses, the primary end point is the abstinence success rate during the final 4 weeks of the trial. This end point is intended to evaluate the efficacy of the DTx intervention in patients with SUD. Statistical significance will be assessed using multiple logistic regression analyses adjusting for stratification factors such as stimulant vs nonstimulant drug use and baseline abstinence status (abstinent vs nonabstinent) as covariates. The treatment effect will be expressed as the adjusted odds ratio for the experimental group relative to the control group along with 2-sided 95% CIs.

Superiority of the experimental group over the control group will be concluded if both of the following criteria are satisfied: (1) the 2-sided *P* value is less than .05, and (2) the lower bound of the 2-sided 95% CI for the adjusted odds ratio exceeds 1.0.

The secondary efficacy end points include (1) abstinence maintenance rate during the 12-week treatment period, (2) treatment retention rate during the 12-week treatment period, (3) total number of abstinent days, (4) longest duration of consecutive abstinent days, and (5) results from psychiatric and psychological assessment tools.

For these outcomes, multiple logistic regression analyses and analyses of covariance will be performed to compare differences between the experimental and control groups.

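### The drug-abuse screening score that every participant completes is not named in the primary model; adding it is a cheap, conditional gain in precision, not the repair of an error

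*Protocol article*

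**What the plan says.** Four places in the Protocol article bear on this.

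- **Textbox 1, Inclusion criteria:** "At screening, completion of the Drug Abuse Screening Test–Korean Version". No scoring, range or cutoff is given, and the test is not called a severity measure.
- **Randomized Controlled Trial:** one pregenerated list, used in order of enrollment. No strata are described.
- **Data Analysis:** the primary test is a multiple logistic regression "adjusting for stratification factors such as stimulant vs nonstimulant drug use and baseline abstinence status (abstinent vs nonabstinent) as covariates". Superiority requires a two-sided P value below .05 and that "the lower bound of the 2-sided 95% CI for the adjusted odds ratio exceeds 1.0". The words introducing the two covariates leave the list open.
- **Discussion, limitations:** "participants were not stratified by severity of SUD". The surrounding text is about showing efficacy in finer severity subgroups and about how hard recruitment is in South Korea. Covariate adjustment is not mentioned.

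**The concern.** As described, severity is handled neither at randomization nor in the named analysis model, although a baseline drug-problem measure is collected from every participant. If that measure predicts abstinence in weeks 9 to 12, two things are given up. A chance difference between arms at baseline goes uncorrected in the odds ratio, and outcome variation that could be explained is left in the error. With 118 participants and a binary endpoint there is little precision to spare.

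Timing matters too. The Results section reports 65 enrolled and an interim analysis already done, in an open-label trial. Starting to stratify the randomization is no longer practical. A covariate can still be prespecified, but one added after database lock would look data-driven.

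**Working it through.** **Inputs from the article.** Participants: "This study aims to recruit 118 participants across 4 regions in South Korea". Design gives 1:1 allocation, so 118/2 = 59 per arm. Alpha is 0.05 two-sided (Data Analysis). Missing abstinence outcomes count as failure, so the analysed number stays near 59 per arm.

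**The plan's own figure.** The 118 is said to be "based on estimates from prior research on the required sample size to demonstrate superiority". The article gives no rates, power or dropout, so it cannot be reproduced. Working backwards at 59 per arm, with

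power = Φ{ [ |p2 − p1| − 1.96·√(2·p̄(1 − p̄)/n) ] / √( [p1(1 − p1) + p2(1 − p2)]/n ) },

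40% vs 65.5% gives (0.255 − 1.96 × 0.0919)/0.0889 = 0.84, which is 80% power. The other 80% power pairs are 20% vs 43.9%, 30% vs 55.3% and 50% vs 74.8%. The detectable difference is therefore about 24 to 26 points.

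**Chance imbalance.** For a standardized baseline score the between-arm difference in means has SD √(2/59) = 0.184. The chance that its absolute value exceeds:

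- 0.20 SD is 28%
- 0.25 SD is 17% (0.25/0.184 = 1.36)
- 0.30 SD is 10%
- 0.40 SD is 3%
- 0.50 SD is 0.7%

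The resulting shift in the log odds ratio is roughly the imbalance times the log of the score's odds ratio per SD. For 0.25 SD this is 0.25 × ln 1.5 = 0.10, 0.25 × ln 2 = 0.17 and 0.25 × ln 3 = 0.27. For scale, at 40% vs 65.5% the treatment log odds ratio is 1.05, with standard error √[1/(59 × 0.24) + 1/(59 × 0.226)] = 0.38.

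**Power.** There were 4,000 simulated trials per scenario, 59 per arm, with a Wald test at two-sided 0.05. The logistic model held treatment, stimulant use and baseline abstinence, and was fitted with and without a standard normal score. Assumed: both binary covariates split 50/50, odds ratio 3 for baseline abstinence and 1 for stimulant use, and a score independent of both. None of these values is in the article.

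| Score odds ratio per SD | 30% vs 55%: without → with | 50% vs 75%: without → with |
|---|---|---|
| 1.0 | 81.4 → 81.4% | 82.6 → 82.6% |
| 1.25 | 81.7 → 82.1% | 82.6 → 83.1% |
| 1.5 | 81.6 → 82.7% | 82.6 → 83.6% |
| 2 | 80.8 → 83.7% | 82.6 → 85.7% |
| 3 | 81.4 → 87.5% | 81.8 → 88.8% |

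The gain is 0 to about 1 point up to 1.5 per SD, about 3 points at 2, and 6 to 7 points at 3. Monte Carlo error on each power is about √(0.82 × 0.18/4000) = 0.6 point. Both models were fitted to the same simulated data, so the differences are steadier than that.

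**Type I error.** With 40% success in both arms, rejection was 4.7 to 5.4% with or without the score. The simulation error is √(0.05 × 0.95/4000) = 0.3 point, so this is consistent with 5%.

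**Change of estimand.** To keep 30% vs 55% marginally, the conditional treatment odds ratio used in the simulation was 3.08 when the score had no effect, and 3.19, 3.40 and 3.87 at 1.5, 2 and 3 per SD. Adding a prognostic score therefore changes the conditional odds ratio being estimated.

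**The case against.** Nothing in the article is invalid or contradictory here. A logistic model with two baseline covariates is legitimate, and the fuller covariate list may sit in an analysis plan that is not shown. Chance imbalance of the size computed is already allowed for in the confidence interval: a 0.25 SD imbalance at 1.5 per SD moves the log odds ratio by about a quarter of its standard error (0.10/0.38). The prognostic strength is assumed, and treating the screening test as a severity score is a reading of it that the article does not state. Baseline abstinence may carry part of the same information, so the gains shown may be too high. All of this stands, and it limits the size of the point.

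The Discussion's limitation is about efficacy across severity subgroups. A reader might infer that adjusting for the score would remove it. It would not: a main-effect covariate says nothing about whether the treatment effect varies with severity. That also stands.

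Lastly, an interim analysis of the primary outcome has been done in an open-label trial, and Ethical Considerations states that no independent data monitoring committee was set up. Changing the confirmatory model now invites suspicion and may need amendment steps. This bears on how the change is made and documented. It is not a reason to leave the covariate list open, because an open list after an interim look invites the same suspicion.

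**Conclusion.** The point holds as an optional, low-cost improvement. A baseline measure that every participant completes is absent from the named primary model, and the covariate list is not closed.

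Two stronger readings are tempting. One is that the omission biases the odds ratio or undermines the test. Randomization protects the comparison, and type I error is nominal either way. The other is that power is definitely being lost. The gain is nil if the score does not predict abstinence, and it reaches 6 to 7 points only at an odds ratio of 3 per SD, a strength the article gives no ground to expect or exclude. The imbalance figures (SD 0.18, 17% above 0.25 SD) follow from 59 per arm alone, but they matter only as far as the score is prognostic.

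The power figures rest on assumed success rates, assumed covariate effects and independence of the score from baseline abstinence.

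**What to change.** Before database lock, replace the open-ended covariate wording in Data Analysis with a closed list: stimulant use, baseline abstinence and the continuous Drug Abuse Screening Test–Korean Version score, in the primary and secondary models. Add a dated statement that the choice made no use of interim results by arm. Report the model with only the two covariates already named alongside it.

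If independence from the interim results cannot be shown, keep the two-covariate model as primary and prespecify the score-adjusted model as a sensitivity analysis. If the unseen analysis plan already closes the list with the score in it, only the article's wording needs to follow.

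Leave the severity-subgroup limitation in the Discussion as it is.

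The cost is one degree of freedom, a somewhat different conditional odds ratio, and documentation of a change made after an interim look, possibly with amendment review. No new data and no further participants are needed.
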